### **Intervention Measures**

**Background:** An unfortunate aspect of a nearly unique focus on large-scale anthelmintic drug administration was, and continues to be, the lack of concern within the global health community for prevention strategies, such as emphases on access to clean water, improved sanitation and hygiene activities that could serve as a backbone of multi-component integrated and sustainable disease control programs. Aiming at an integration and sustainability of parasite control program requires a package of intervention activities that are readily tailored to a given endemic setting and are fine-tuned over time. In this study, different intervention packages will be implemented considering the environment and the interrelated demographic, health and social systems contexts in the study area.

### **Hand Washing With Soap**

High prevalence rates of intestinal parasites transmitted through faecal-oral route demonstrates the role played by unhygienic hands in transferring fecal particles from one host to another. Based on our preliminary survey, more than 89% of the children does not use soaps during hand washing and about 41% never wash their hands after defecation. These inadequate hand hygiene practices may transfer pathogens through direct interpersonal contact, contact with inanimate objects and surfaces, and during food preparations. Furthermore, in such setting, where the households store water they use for cooking and drinking in the house, dipping contaminated hands into storage containers can also transfer pathogens to other family members.

Hand-based transmission of pathogens is so ubiquitous that hand washing with soap has been argued to be the best intervention to prevent diarrhoea, and the most cost-effective option for prevention of morbidity and mortality in children.

Most people, especially children, do not wash their hands with soap at important times, such as after using toilet and before eating. The quantity and proximity of water available to households have been demonstrated to correlate with frequency of hand washing. Unfortunately, large proportion of people in developing countries do not have household-level access to piped water, which presents a formidable challenge to increase rates of hand washing with soap and water in such communities.

**Methodology:** Small bars of plain soap will be provided to each household with child in the hand washing with soap intervention and will be replenished as necessary. Children and family members in the respective group will be encouraged to wash their hands with water and soap before meals, after defecation, after playing on the ground and touching animals, before and after preparing food (mothers) and when ever their hands get unclean. Brief clarifications will be given on the clinical importance of intestinal parasitic infections and methods of prevention; proper hand washing procedures will be demonstrated during the commencement of the study and at every visit.

**Training:** Field workers will be trained for two days on the proper hand-washing with soap and nail clipping techniques, the purpose and procedures of the visits, supervisory activities, fellow-up, data collection, and reporting.

Study participants will be visited every week by data collectors and the investigator to determine compliance with hand hygiene, to answer any question, re-educate on the importance of hand hygiene and go over specific hand hygiene procedures.

### **Wash Your Hands: The Right Way**

#### **How to Wash**

1. Wet hands and wrists
2. Apply soap
3. Lather for 45 seconds. Make sure you scrub in between fingers, the back of your hands, finger tips and wrists (**This is a VERY important step.**)
  - A song related to hand-washing that the children sing in their school ‘let’s wash our hands with water and soap’ will be adjusted to fit the 45 seconds and children will be made to sing the song to keep the time needed to rub their hands.
4. Rinse

## 5. Dry your hands

- Wet your hands with clean, running water and apply soap
- Rub your hands together to make lather and scrub them well; be sure to scrub the backs of your hands, between your fingers, and under your nails.
- Continue rubbing your hands for at least 45 seconds. Need a timer? "Let's wash our hands with water and soap" song – the first beginning to end once.
- Rinse your hands well under running water.
- Dry your hands using a clean towel or air dry them.

## When to Wash

- After using the toilet
- Before eating and feeding children
- Before, during, and after preparing food
- Before and after caring for someone who is sick
- After cleaning up a child who has used the toilet
- After touching an animal or animal waste
- After touching garbage
- After touching soil
- After blowing your nose, coughing, or sneezing

[figure not shown]

Fig. 1. Steps to be followed during washing hands with soap.

### **Hand Finger Nail Clipping**

Studies have been able to isolate disease causing microorganisms from swabs of nails and nail clippings. Keeping nails clean and dry avoids collection of bacteria and other infectious organisms under the nails. Cutting nails short and washing hands by scrubbing nails after using the toilet and before meals has been shown to protect children and family from recurrence of parasitic infections. Preliminary data from our preliminary survey shows nail hygiene is of concern in school-aged children where 58.9 % of the children had unclipped finger nails and 49.1% of these nails were unhygienic.

**Methodology:** Children in the finger clipping intervention group will be provided with new nail clippers. Nail clippers will be kept by the field workers that will frequently visit the households to determine compliance with the intervention protocol, re-educate on the importance of nail trimming and go over specific nail clipping procedures. Each clipper will be kept tagged with codes for each child. Nail clipping will be performed by the health workers at weekly bases.

#### **2.1. Procedure of nail clipping**

- Cutting fingernails is easy. Just make sure you have a nice, sharp (**and above all safe**) nail cutter and a wastebasket to collect the nails
- Cut the nails straight across until they no longer extend over the finger, so that they don't show any white
- Follow the shape of the fingertip when trimming finger nails
- Do not cut the nails uneven, this may cause nails to split and crack and hence accumulate dirt and pathogens
- Look the nails over to ensure that they are all of the same length and shape, and also that they're smooth and not uneven or pointy. Keep clipping and filing until they all look the same and are smooth. Once they are, you're done!

**Control condition:** Control households will be provided with a regular monthly supply of sugar in an effort to preserve willingness to participate, but they will be given no products that would be expected to affect their hand-washing and nail clipping behaviours. They will be neither encouraged nor discouraged for hand-washing and nail clipping. Control households will be visited at equal frequency with the intervention households. Control

households will also frequently checked for the presence of soap for hand-washing and nail clippers during the weekly visits to check for contamination.

### **Sample collection and Analysis following 6 months intervention**

#### **Parasitological examination**

- Following 6 months intervention children will be made to come to the schools where the laboratory will be established.
- A thumb sized fresh stool specimens will be collected on the spot from all the study subjects.
- Children will be provided with:
  - clean labelled plastic screw-top containers (for sample collection)
  - plastic sheet (to catch the stool in the toilet)
  - applicator stick (to transfer the sample).

Stool analysis will be done using:

- Direct saline wet mount
  - Formalin ethyl-acetate concentration technique
  - Kato-Katz technique (thick smear 41.7mg)
- Duplicate slides will be prepared for each stool specimen and for each of the techniques used.
- A child will be classified as re-infected if an infection was detected by any methods used.
  - 10% of randomly selected stool smears will be re-examined for each sample collected for quality control purposes.

#### **Haemoglobin survey**

- At the end of the six months follow-up, haemoglobin concentration will be determined in finger prick blood using a HemoCue analyzer at the spot (HemoCue Hb 201z, Sweden).
- One day training of technicians collecting and analyzing blood samples
- Daily check of the HemoCue using reference microcuvettes based on the manufacturer instructions.
- Haemoglobin readings will be adjusted for altitude, and anemia will be defined for respective age and gender groups based on the World Health Organization cut-off values.

## **Data Processing and Analysis**

Data will be entered and processed on an appropriate software and will be analysed using appropriate statistical analysis methods. Effectiveness of interventions will be assessed using regression models by odds ratio with help of SPSS version 16 software. Effectiveness of an intervention will be estimated based on a comparison of all individuals allocated to receive a particular intervention package versus those allocated not to receive the intervention. Infection intensity differences between intervention and control arms will be analysed by arithmetic mean differences for the egg counts using the independent-samples t-test. Participants will be analysed according to the group to which they were randomized. Base-line demographic and hygiene information will be obtained using structured questionnaire. Questionnaires will be coded by investigator and statistician, and data entry will be done using an appropriate statistical software. Statistical significance will be tested with  $\chi^2$  and shall be set at  $p < 0.05$ .

**Problems and pitfalls:** The study is expected to have limitations arising from the study design to be followed, the process of data collection and nature of the study respondents. As behavioural trials are difficult to be blinded, systematic error is expected to occur due to the lack of blinding. An attempt to reduce this effect will be made by masking field workers to the identity of the assigned interventions and the outcome of interest. Field workers will check the presence of soap for hand-washing in the households other than those assigned to hand-washing intervention, and nail clippers in households other than assigned to the intervention during their weekly visits in an attempt to check for contamination.

Loss-to-follow-up will be reduced, and compliance during follow-up will be enhanced by recruiting children and households who are interested and reliable in to the selection process, and by arranging frequent contacts with individual members of the families.

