### **Sample size determination**

Using the formula for ‘comparison of proportion of successes’ and assuming equal groups; based on data collected previously in the study area on prevalence of intestinal parasitosis among the age-group (72.2% -data from previous prevalence study in the area) and assuming prevalence reduction of 20%; taking a power of 80% and assuming a significance level of 0.05; the sample size per group (intervention and control) will be 90 households.

$$n = \frac{\left\{ \begin{array}{c} \text{success x failure} \\ \text{on treatment A} \end{array} \right\} + \left\{ \begin{array}{c} \text{success x failure} \\ \text{on treatment B} \end{array} \right\}}{(\text{success on A} - \text{success on B})^2} \times \text{‘magic number’}$$

Sample size = 88 (90); 90 households in intervention and 90 household in the control arm (n=180). Considering 20% loss-to-follow up = 180 + 36 = 216 households.

|                             |     | Nail clipping (NC) |     |       |
|-----------------------------|-----|--------------------|-----|-------|
|                             |     | Yes                | No  | Total |
| Hand washing with soap (HW) | Yes | 54                 | 54  | 108   |
|                             | No  | 54                 | 54  | 108   |
|                             |     | 108                | 108 | 216   |

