### Requirement of parasite free children

Prior to random allocation to the intervention and control arms and following acquisition signed informed consent, children will be screened for intestinal parasitosis. Children screened positive for intestinal parasitic infections will be treated using standard treatment regimen. Parasite negative children in the respective households will be randomly assigned into different intervention and control groups and randomisation will be by sealed envelope method.

[figure not shown]

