Fieldworkers will be trained on approaches to promote hand washing and hand nail clipping, standard procedure of hand washing with soap, data collection and reporting. Fieldworkers will visit households on a weekly basis throughout the study period to encourage hand washing, nail clipping and to record incidence of clinical symptoms. Same regular visits will be made to the control households. Sociodemographic data will be collected prior to the initiation of the study using structured questionnaire.

**Data collection and processing:** A series of parasitological screening activities will be done after completion each treatment phase based on the life cycle of each identified parasite species until parasite positive children are screened negative. Children who received hand washing with soap will be compared with children who received no hand washing and children under nail clipping intervention will be compared against the non clipping group. Differences of impact in different subgroups and possible interactions between the different intervention activities (hand washing with soap and nail clipping) will be analysed.

The aim of the study and procedures employed will be discussed with the local administrative leaders and health authorities, and with parents and children participating in the study.

Quality of the tests and accuracy of egg counts of each parasitological analysis period will be assessed by screening a random sample of 10% of the slides for a second time by a well-experienced laboratory technologists.

**Anticipated results:** The primary outcome measures will be:

- the proportion of children with reduced intestinal parasitosis re-infection rates in the intervention and control arm
- the proportion of children with reduced parasite load (infection intensity) rates in the intervention and control arms

The secondary outcomes will be:

- the proportion of children with reduced prevalence of anemia in the intervention and control arms

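### The t-test planned for mean egg counts gives intervals that tend to understate a real reduction, loses some power, and treats children from the same household as independent

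*Protocol*

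**What the plan says.** - **Outcome.** Specific Aim I (Anticipated results) lists two primary outcomes. The second is "the proportion of children with reduced parasite load (infection intensity) rates in the intervention and control arms".
- **Test.** Data Processing and Analysis states that intensity differences between arms will be "analysed by arithmetic mean differences for the egg counts using the independent-samples t-test". The same section speaks generally of suitable methods, but for egg counts it names this test and no transformation, count model, permutation or bootstrap step.
- **Starting state.** Under the requirement of parasite-free children: "Parasite negative children in the respective households will be randomly assigned into different intervention and control groups".
- **Unit.** The opening section takes two children from any selected household with more than one in the age range. The opening section and the methodology of Specific Aim I randomise households. The parasite-free section words assignment in terms of children, but the four-arm allocation is described at household level and I read it so.
- **Measurement at 6 months.** Three stool techniques are used, and only the Kato-Katz smear has a stated stool weight. For re-infection: "A child will be classified as re-infected if an infection was detected by any methods used".
- **Sample size.** It is derived for prevalence only, starting from "72.2% -data from previous prevalence study in the area". No power is given for egg counts.

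**The concern.** Six-month egg counts in children who began uninfected are a block of zeros plus a right tail. A few heavy infections then dominate both the arm means and their standard errors. When the sample happens to contain few heavy counts in the control arm, the estimated difference and its standard error are both too small. The symmetric t interval then sits too low and is too narrow. A real reduction in a primary outcome could be missed or reported as smaller than it is.

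Separately, two children in one household share exposure and allocation. A test that counts them as independent overstates the information in the data.

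**Working it through.** **1. The plan's own figure.** Inputs from Sample size determination: 72.2% in controls, a reduction of 20 taken as percentage points (52.2%), 80% power, two-sided 0.05 (inferred, multiplier 7.85).

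n = [0.722 × 0.278 + 0.522 × 0.478] / 0.20² × 7.85 = 0.4502 / 0.04 × 7.85 = 88.4

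This matches the stated 88, rounded to 90. It covers prevalence, not counts.

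**2. Minimum share of zeros.** On those prevalences, 1 − 0.722 = 27.8% and 1 − 0.522 = 47.8% of children are uninfected and count zero. These are minima, because a child found positive by another technique can still have an egg count of zero.

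**3. Interval and power, one child per household.** The Protocol gives no egg-count mean or dispersion, so the mean m and dispersion k below are assumptions. Counts are negative binomial with 90 per arm. The zero share in an arm is (k/(k+m))^k; for example (0.05/5.05)^0.05 = 79% and, after an 80% reduction, (0.05/1.05)^0.05 = 86%.

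| Control mean, k, true reduction | Zeros, control / intervention | Coverage of 95% t interval | Power, t-test | Power, permutation test of the mean difference |
|---|---|---|---|---|
| 5, 0.05, 80% | 79% / 86% | 85% | 42% | 54% |
| 10, 0.1, 70% | 63% / 71% | 88% | 58% | 64% |
| 10, 0.2, 60% | 46% / 54% | 93% | 72% | 73% |

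The power gaps are 12, 6 and 1 points. Simulation error is a point or two: repeat runs put the t-test in the first row between 39% and 43%. In that row the misses were 14.8% on the side that understates the benefit and 0.2% on the other.

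**4. False positives, one child per household.** With a control mean of 20 and no effect, the t-test rejected 3.4% (k = 0.05), 4.5% (k = 0.1) and 5.0% (k = 0.3). It is not anti-conservative here.

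**5. Two children per household.** With within-household correlation ρ and pairs throughout, the variance of an arm mean is 1 + ρ times what the t-test assumes. In large samples the true type I error is 2 × [1 − Φ(1.96/√(1+ρ))].

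- ρ = 0.3: 1.96/1.140 = 1.72, giving 8.6%.
- ρ = 0.6: 1.96/1.265 = 1.55, giving 12.1%.

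Simulated skewed counts gave about 7% to 12% over the same range. Both ρ and the use of pairs in every household are assumptions; the Protocol gives neither a correlation nor the share of households with two children.

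**The case against.** The strongest reply is that a t-test with 90 per arm is robust, that the arithmetic mean is a sensible target, and that the size of the problem rests on assumed dispersion. Much of this stands.

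- **Mostly zeros.** A reader might infer that counts will be mostly zero. The documents do not say so: on their own prevalences 52% to 72% of children are infected, and no species mix or egg count is given. With 28% zeros and k = 0.3, coverage was 93% to 94% in the runs with a real effect, and a negative binomial test gained at most 4 points of power.
- **A very large power loss.** Set against a negative binomial likelihood-ratio test, the first row shows 39% versus 63%. That contrast is not like for like. The t-test rejects 3.4% to 4.5% under no effect and the other test 5% to 7%; with both calibrated to 5% the figures are 52% and 60%. The data also came from the competitor's own model. Larger gaps seen for rank or log-scale tests under lognormal counts partly reflect a different target quantity.
- **False positives.** One might conclude that skewness inflates them. It does not; only household pairing can.
- **Unequal variances and one factor at a time.** With equal arms, pooled and Welch tests had the same power within a point. In a balanced factorial whose primary comparisons are main effects, a marginal comparison is not biased.

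What remains is the interval's one-sided under-coverage, a power loss that depends on dispersion, and the neglect of household pairs.

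**Conclusion.** The point holds as a moderate weakness in the analysis of a primary outcome. Under assumed negative binomial counts with one child per household, the t interval covers about 85% to 93% under a real effect and errs towards understating the reduction. Power is about 1 to 12 points below a valid permutation test. Type I error is sound with one child per household and about 7% to 12% in the upper case of correlated pairs throughout.

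That zeros will occur, and that pairs can enter, follows from the Protocol. How much this costs does not, because the Protocol gives no egg-count mean, dispersion or household correlation. The choice of the arithmetic mean is not at fault. The wording of the outcome as a proportion while the test compares means is a separate mismatch.

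**What to change.** Replace the t-test sentence with a specification along these lines:

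- **Target:** arithmetic mean egg count at 6 months, zeros kept, in all randomised children with a 6-month stool result, with terms for hand washing and nail clipping.
- **P-value, in all cases:** a permutation test that re-allocates whole households, for each factor within levels of the other and respecting any blocking. Do not make it conditional on few positives, since that would let the data choose the test.
- **Estimate:** the difference or ratio of arithmetic means with a 95% bootstrap interval that resamples households within the four groups. State the bootstrap type in advance.
- **Role of a model:** negative binomial regression may supply the ratio, but its Wald or robust p-value should not be the primary test. A robust Wald test of the log mean ratio rejected about 7% to 10% under no effect in these settings.
- **Not a rank test by default:** with mean 20, k = 0.1 and a mean ratio of 0.3 it had 28% power against 58% for the t-test.

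Cost: some extra programming, probably outside SPSS 16, and no new data or children. Two limits should be stated. If counts are only mildly dispersed, the gain is small. And a bootstrap resamples the same few heavy counts, so it should not be presented as fully restoring 95% coverage; its coverage is worth simulating before the method is fixed.

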## **9. Inclusion and exclusion criteria**

### **Inclusion**

- children who are able to bring signed written informed consent
- children / households who agree to participate throughout the study period
- children who permanently live in the area and who are going to stay in the household throughout the study period
- children aged 6 to 15

**Exclusion**

- children who are not able to bring signed written informed consent
- children with known mental problems and sever physical handicap
- age less than 6 and above 15 years

**Potential Risks**

No major risks are expected to be associated with this study. Minor side effects like abdominal pain, nausea, vomiting and diarrhoea might be seen in heavily infested children following provision of treatment.

